### Variables to predict LOS and gut dysbiosis

Variables have been selected based on a literature search and local clinical experience. Table 1 shows factors predicting LOS and gut dysbiosis that will be captured during the study period. Independent variables will be categorized as socio-economic, neonatal, maternal, and septic risk factors (Table 1).

**Table 1 pone.0325099.t001:** Candidate variables for predicting LOS and gut dysbiosis.

Socio-economic factors	Neonatal factors	Maternal factors	Septic risk factors
Maternal education level	Gestational age	Age at delivery	Invasive ventilation
Self-rated household income	Sex	Parity	Central line at least 48 hrs
Family health insurance	Birth weight	Previous stillbirths	Parenteral nutrition
	Multiple births	HIV status	Presence of any maternal risk factors
	APGAR score at 1 minute	Medical conditions	Type of feeding
	APGAR score at 5 minutes	Pregnancy complications	
	Place of birth	Maternal antibiotic exposure 3 months before delivery	
	Delivery complications		
	Antibiotic exposure and type		
	Type of delivery		

During the observational period of 28 days clinical signs and symptoms of LOS and/or NEC, BC results with phenotypic identification, and antibiotic susceptibility testing, the previous use and type of antibiotics, and the clinical outcomes, will be recorded by the study team in electronic data capture forms. Stool samples for microbiome analysis will be collected in a standardized manner on day 1–3, and days 7, 14, 21 (each ±3) and neonates’ type of feeding in the last 24 hours will be categorized as exclusive human milk (no formula given), breastfed mainly (>80% feeds breastmilk/human milk), formula feed (>50% of feeds include formula), only formula (no human milk), or no enteral feeding at all.

### Data collection team, study period and timelines

Data will be collected by a dedicated study team, consisting of a local medical officer and two study nurses (trained nurse attendants), under the coordination and supervision of a study coordinator – a pediatrician working in the neonatal unit. To ensure seamless collaboration, all neonatal unit staff will be informed and educated about the clinically based survey. This collaborative approach will support effective recruitment, sampling, and adherence to national treatment guidelines, ultimately enhancing clinical care. The study began on October 23, 2023, and is planned to run for two years. Participant recruitment will span 18 months, followed by six months dedicated to stool sample processing and gut microbiome DNA sequencing. Analysis of clinical data and microbiome profiles will commence immediately afterwards.

### Data collection tools and methods

All study data will be pseudonymously recorded and collected using password-secured tablets and managed using REDCap^®^ electronic data capture tools [33,34]. Patients will be screened for inclusion and if recruited a copy of the study admission form will remain in the patient`s file to avoid re-recruitment. Study team members will enter the data at recruitment, at times of sample collection, during each episode of sepsis or NEC, and discharge/referral or death, including information from microbial reports and other laboratory results into the eCRFs. At the end of follow-up all co-morbidities and complications will be evaluated and recorded. All data points will be checked by another study member, validated and approved by the study coordinator or local PI.

### Demographic and clinical parameters

Properly designed eCRFs will be used to collect relevant information from the mother and the preterm neonate. Information will be obtained from the maternal medical records, admission form, direct interview with the mother, and examination of the preterm neonate on admission and during their hospital stay. Maternal medical charts will be reviewed for the GA estimation using the best available information either the last menstrual period (LMP) or early obstetric ultrasound, whichever is available. The participants’ weight at admission and throughout the observation period will be measured using a calibrated SECA^®^ medical scale (UK), with readings recorded to the nearest whole number in grams. The scale will be calibrated daily to ensure accuracy. Concurrently we will perform a New Ballard Score (NBS) for those preterms recruited within 48 hours to confirm the GA recorded. In addition, we will take the foot length during NBS examination to analyse it as a proxy for GA assessment in comparison to valid data like the early obstetric ultrasound or LMP.

Once recruited, initial demographic, pregnancy, and birth history, maternal risk factors will be recorded and the preterm neonate be followed up daily for 28 days after birth for routine newborn care and any of the outcomes of this study. If the preterm neonate is discharged before the 28-day follow-up period, all attempts will be made to monitor them during their scheduled weekly outpatient clinic visits, where they will undergo clinical assessments for any signs of sepsis. If sepsis is suspected, they will be readmitted for appropriate care. At day 28 of life, a phone call will be made to those that were prematurely discharged to assess if the infant is alive and if there was any readmission due to suspected sepsis.

### Samples collection

#### Blood cultures.

To describe the etiological agents and AMR patterns of neonatal bloodstream infections, we will be collecting 1–2 ml sterile blood for cultures [35] in BD BACTEC™ Peds Plus BC bottles according to international recommendation guidelines in all participants developing signs and symptoms of LOS or NEC [36], without delaying antimicrobial treatment. For participants at risk of developing early onset sepsis (EOS), termed as presumed EOS according to standard treatment guidelines, and started on antibiotics based on risk factors, BCs will also be taken free of charge before initiation of treatment whenever possible. Another BC will be taken in cases of switching, adding, or escalating antibiotic therapy. An episode of sepsis will be classified as culture-proven sepsis or clinical sepsis depending on BC results and additional clinical information by the study physicians. The blood culture samples will be processed in the microbiology laboratory at MNH which is certified in accordance with the international standard (ISO 15189:2022).

#### Isolation and identification.

BC bottles that have been inoculated will be sent to the laboratory as soon as possible by the study nurses, or stored at ambient temperatures if transport to the lab is delayed. Once BC bottles are received in the microbiology laboratory, registration follows whereby BC bottles are given the unique ID number and loaded into the automated BACTEC^®^ system (BACTEC® 9050; Becton Dickinson) for incubation and monitored for a maximum of five days to observe bacteria growth. For each positive BC, a primary gram stain will be performed and communicated to the clinician as soon as possible. Organisms will be sub-cultured on Blood Agar (BA), MacConkey (MCA, Oxoid, UK), and or Sabouraud Dextrose Agar (SDA) if the primary gram stain observed the presence of budding yeast cells microscopically. Organisms will be identified based on their colonial morphology and biochemical characteristics as described by Murray et al. (30). Gram-negative organisms will be identified using oxidase, Kliger Iron Agar (KIA), sulfur indole and mobility (SIM), a urease, and citrate test, while gram-positive organisms will be detected by catalase reaction, coagulase test, DNase test, and bile esculin test (30). Analytical Profile Index (API) 20E and API-20 NE (BioMérieux, France) tests will be used to confirm isolates in case of ambiguity.

#### Antimicrobial susceptibility pattern.

Antimicrobial susceptibility testing (AST) of the bacterial isolates will be done by the conventional Kirby-Bauer disk diffusion method as per Clinical Laboratory Standard Institute (CLSI) guidelines. AST will be done for antibiotics that stand as the first, second, and third line agents used to treat neonatal sepsis in the Tanzania treatment guidelines and used at MNH; which are ampicillin, cloxacillin, aminoglycosides (gentamycin and amikacin), and cephalosporins (cefotaxime, ceftriaxone and/or ceftazidime), fluoroquinolone (ciprofloxacin), amoxicillin-clavulanic acid, piperacillin-tazobactam, and carbapenem (meropenem). Ceftriaxone/Sulbactam will be tested using an E-test for Gram-negative bacteria. In the case of Gram-positive bacteria, it is recommended to use vancomycin if all tested antimicrobial agents are resistant. In addition, the combination disc diffusion method will be performed for detection of ESBL-producing Gram-negative organisms, Inducible Clindamycin Resistant (ICR) and MRSA/MRCoNs also tested for Gram-positive isolate according to CLSI guidelines. AST results will be reported as sensitive, intermediate, and resistant. Intermediate results will be considered resistant during analysis. Blood culture and AST results will be recorded, including clinical information as described in the eCRF. These results will be immediately communicated to the attending physician for management of the preterm infants.

#### C-reactive Protein.

During a sepsis episode, C-reactive protein (CRP) will be taken as part of the laboratory workup using the Architect c8200 clinical chemistry analyzer. CRP result >10mg/l will be considered high and indicative of infection/inflammation.

When suspecting early-onset sepsis, CRP is routinely taken 48 hours after birth as part of the SOP of the NCU, as one of the parameters used to guide antibiotic treatment. If the CRP is high, antibiotics will be continued or changed depending on the clinical condition of the neonate while awaiting the BC results. If it is low, and the patient is clinically well and BC is negative, antibiotics are stopped and sepsis is ruled out.

For LOS, CRP is usually taken during or close to the sepsis episode and is interpreted as one of the diagnostic markers. The CRP taken during or closest (within 48 hours) to the sepsis episode will be recorded.

#### Gut microbiome analysis.

To investigate gut fresh fecal samples will be obtained from soiled diapers in disposable sterile tubes, as fresh as possible, and preserved using PowerProtect^®^ DNA/RNA buffer (QIAGEN GmbH, Hilden, Germany) as per the manufacturer’s guidelines. Following SOPs within 20 minutes of collection samples will be placed in a cooling box maintained at temperature of 4–6°C, and transported to the Central Pathology Laboratory at MNH, which is about 7 minutes’ walk where they will be stored in a −80°C freezer within 4–6 hours. The mother will also be asked to provide a stool sample within the first few days postpartum using the same collection and storage protocols. DNA extraction from samples will be performed at MUHAS microbiology laboratory and an aliquot of frozen DNA samples will be transferred to Germany for shotgun metagenomics (for details please see S1 File), all in compliance with national regulations (NIMR Material Transfer Agreement) and international guidelines (Nagoya Protocol). Necessary permissions for sample transfer will be strictly adhered to. Samples will be stored for 5 years after completion of the study before destruction. Data will be kept for 30 years according to international standards.

### Investigation tools’ validity and reliability of the data

All data collection tools will undergo pre-testing during a pilot phase involving at least ten participants before the full study begins. Before the project launch, the entire unit will be briefed on the study’s aims and objectives to ensure that all staff adhere to uniform procedures and standards of care for the vulnerable populations involved. Research assistants will receive training in Good Clinical Practice (GCP), research ethics, and the proper use of study tools, including the REDCap^®^ data management system, to ensure accurate data collection. Continuous training on hygiene, aseptic techniques for drawing and storing blood culture samples, and infection prevention measures will be conducted to minimize contamination and maximize sample yield. Data quality will be regularly monitored by the PIs, study managers, and data managers through reports, data exports, and statistical checks to maintain consistency. All data entries will be cross-checked by another study team member and validated by the study coordinator. A robust data management system led by experienced data managers and the research team will be used to clean and export data for analysis in R statistical software, ensuring the accuracy and integrity of the collected data.

Data entry will be performed by authorized research staff using touch-screen tablets equipped with the REDCap^®^ data management system to allow real-time data entry. Additionally, a customized Android application for the tablets will be utilized locally to manage participant registration, appointment schedules, and sample storage. Entered data will be securely transmitted to servers located at MUHAS and the German site. These main servers will only be accessible to the data managers and PIs on request.

For data validation and resolution, the data management team will conduct monthly reviews using established quality checks to identify discrepancies, missing fields, or logic errors in the collected data. Any issues found will be communicated to the research team for resolution. An automated audit trail will track all corrections, ensuring transparency and accountability throughout the data management process.

### Statistical analysis

Descriptive statistics will be used to summarize the demographic and clinical characteristics of the study population, including gestational age, birth weight, gender, mode of delivery, and presence of comorbidities. Mean and standard deviation or median and interquartile range for continuous variables will be used and for categorical data frequencies or proportions will be described.

To answer the first objective on the incidence and risk factors of LOS, the incidence density will be calculated as the number of new cases of LOS divided by the total person-time at risk in the cohort. The person-time at risk will be calculated by summing the individual follow-up durations until the occurrence of BC-proven LOS (clinical sepsis, NEC, and death).

Cox-proportional hazard regression will be utilized to investigate the relationship between the risk factors and risk to develop primary and secondary endpoints. First, we will perform univariate cox-regressions for potential risk factors to identify individual risk factors, all variables considered relevant for the study question will be included in the multivariate cox-regression to adjusting for potential confounders. The hazard ratios (HRs) with the 95% confidence intervals (CIs) will be estimated for each risk factor. Etiological agents of LOS/NEC and the respective AMR patterns will be described as the proportion of isolates resistant to each antibiotic and according to international standard.

Microbiome analysis will be performed to evaluate gut dysbiosis in preterm infants prior to the development of LOS and in relation to the microbiome of the mother. Association of relative abundances of microbial species with the factors of gestational age, days of life, diet, and LOS will be limited to species that were found with a non-zero relative abundance in at least 40 stool metagenomes. Square root-transformed relative abundancies will be used and analysed using linear mixed effect (LME) models, where repeatedly collected microbiome data from each child is considered to cluster.

Antibiotic interventions following a LOS diagnosis are likely to have a strong impact on the microbiome composition. Statistical analyses will be performed using the latest version of R statistical software. Cox regression will be calculated using the *survival* package and LME using the *lme4* package. In all above-mentioned association tests, samples taken after LOS diagnoses will be excluded from the statistical analysis since the present study focusses on the microbial pattern that precedes LOS.

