## Materials and methods

### Study design

This study will be a case-control study nested into a hospital-based, single-center, observational neonatal cohort. Recruited preterm neonates will be followed over their first 28 days of life. The primary clinical endpoint in this study is a blood culture (BC)-proven LOS. Secondary endpoints are clinical sepsis, NEC, death to clinical and/or BC-proven sepsis or NEC, death to any cause, or discharge from the hospital with or without sequelae.

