### Study population and sample size

The study participants will include inborn and outborn preterm neonates born at 28 + 0 to <34 weeks of GA admitted to the neonatal wards, and their respective mothers who consented to participate after a detailed description of the study has been given by trained study team members. Recruited preterm neonates should have a minimal weight of at least 1000 g and be enrolled within their first week of life. We will exclude infants whose mothers are below 18 years of age, have severe, life-threatening illness at the time of admission, and/or have severe comorbidities or severe congenital malformations. Furthermore, neonates or mothers who ever received probiotic supplements during pregnancy will be excluded from this study.

Sample size calculations considered all study objectives and the one requiring the largest sample size will be the basis to determine recruitment numbers. All eligible preterm neonates admitted to the neonatal unit during the 18-month study period will be recruited and closely followed up for 28 days each.

To answer the primary research question on the hypothesis of preterm neonates developing gut dysbiosis before the onset of sepsis we need to identify preterms with BC-proven sepsis, assess their microbiomes, and compare it with controls (matched for GA, sex, mode of delivery, type of feeding, and previous antibiotic exposure). Assuming a rate of BC-proven sepsis of 10% and 25% missed samples we expect to identify 72–135 bloodstream pathogens (positive BCs) with 54–101 complete sets of stool samples for microbiome analysis within 18 months [7,10]. According to Graspeuntner *et al.,* we then expect gut dysbiosis in 30% of the neonates without and 60% of the children with LOS [19].

Our minimal sample size considerations are based on the proportions of gut dysbiosis in children with and without LOS. Assuming an alpha level of 5% and a power of 80% a minimal study number of 84 children (42 with and 42 without LOS) is needed to reject the null hypothesis that no difference in the proportion of dysbiosis between both cases and controls. Cases are defined as preterm neonates who develop LOS and controls as preterm neonates who do not develop any clinical or culture proven sepsis during the observation period (after 72 hours of life).

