### Definitions of LOS, culture proven sepsis, clinical sepsis and NEC

LOS is defined as a bloodstream infection occurs after 72 hours of life, typically caused by nosocomial or community-acquired pathogens [26]. Culture-proven sepsis is identified when a bacterial or fungal pathogen is isolated from a sterile site, such as blood or cerebrospinal fluid. In contrast, clinical sepsis is diagnosed based on clinical signs and symptoms consistent with sepsis in the absence of a BC [27]. The signs and symptoms of neonatal sepsis range from nonspecific manifestations to hemodynamic collapse, requiring a high index of suspicion for timely diagnosis. This study will uniformly apply the WHO criteria for neonatal sepsis, which offer a standardized approach for identifying sepsis in preterm neonates [28]. LOS will be defined by the following criteria by responsible physicians, at least the presence of two signs as per WHO which includes difficulty feeding, convulsions, lethargy, tachypnoea, severe chest indrawing, hypothermia, hyperthermia, bulging anterior fontanelle and skin or umbilical infection with pus requiring systemic antibiotics for at least five days [28].

Cases will be categorized as culture-proven sepsis and clinical sepsis. Instances of positive BCs without accompanying signs or symptoms will be considered contaminants. Specifically, coagulase-negative staphylococci (CoNS) will be classified as a pathogen only if overt signs and symptoms consistent with sepsis, as defined by WHO criteria, are present; otherwise, CoNS will be regarded as contaminants [29]. To improve diagnostic accuracy where available, C-reactive protein (CRP) levels will be used as a biomarker during suspected sepsis episodes, with elevated levels supporting the presence of an inflammatory response [30].

In this study, NEC is defined and suspected clinically based on the presence of one or more of the most characteristic clinical features including abdominal distension, feeding intolerance, bilious vomiting or gastric aspirate and bloody stools, and if available, complemented by the finding on abdominal imaging of intramural gas, pneumoperitoneum or sentinel bowel loops [31,32].

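### Person-time at risk for late-onset sepsis includes the first 72 hours of life, when the event cannot occur by definition, so the planned incidence density is modestly understated

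*Protocol article*

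**What the plan says.** All references are to the protocol article.

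- **Rate (Statistical analysis).** For what it calls the first objective, "the incidence density will be calculated as the number of new cases of LOS divided by the total person-time at risk in the cohort".
- **Denominator (same section).** "The person-time at risk will be calculated by summing the individual follow-up durations until the occurrence of BC-proven LOS", followed by a bracket that names clinical sepsis, NEC and death. No start point is given, and the first three days are not removed.
- **Event (Definitions of LOS, culture proven sepsis, clinical sepsis and NEC).** "LOS is defined as a bloodstream infection occurs after 72 hours of life".
- **Entry (Study population and sample size).** Infants must "be enrolled within their first week of life".
- **Length of follow-up, in three wordings.** Study design: "Recruited preterm neonates will be followed over their first 28 days of life". Demographic and clinical parameters: once recruited, "the preterm neonate be followed up daily for 28 days after birth". Study population and sample size: "closely followed up for 28 days each".
- **Cox models (Statistical analysis).** These are planned for primary and secondary endpoints. Neither a time scale nor an entry rule is named.

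**The concern.** An incidence density is cases divided by the time during which a case could have been counted. Before 72 hours no bloodstream infection can be classed as LOS, so that time adds to the denominator and can never add to the numerator. The plan expects enrolment in that window: the first stool sample is scheduled for days 1-3, and the New Ballard Score is done in infants recruited within 48 hours.

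The size of the error depends on when follow-up starts, and the three wordings do not settle this. Counted from birth, follow-up also includes days before enrolment, during which the infant had to survive to join the cohort. Counted from enrolment, only the time before 72 hours is surplus. The third wording, read literally as 28 days from enrolment, would take an infant enrolled on day 7 to day 35.

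At stake is a rate that will be compared with other units. A rate with the first three days in its denominator is not comparable with one counted from 72 hours.

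**Working it through.** **The plan's own figures.** The article states no incidence density or person-time total. Its expected yield does reproduce: 40 × 18 = 720 and 75 × 18 = 1350 infants; at the 10% it assumes ("Assuming a rate of BC-proven sepsis of 10% and 25% missed samples"), 72 and 135 cases. The 10% is carried forward.

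**Inputs.** From the article: 10% LOS, event possible only after day 3, entry on days 0-7, end at day 28, and a peak between the second and third week. Assumed, because the article does not give them: mean onset between day 10 and day 21, entry age uniform over the first 1, 2, 3 or 7 days, and no death or loss.

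**Step 1. All enrolled by 72 hours, clock at birth (720 infants, 72 cases, 648 non-cases).**

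- Onset day 10. Birth clock: 72 × 10 + 648 × 28 = 18,864 days. From 72 hours: 72 × 7 + 648 × 25 = 16,704 days. Rates: 72/18,864 = 3.82 and 72/16,704 = 4.31 per 1000 days. Ratio 0.886.
- Onset day 21. Birth clock: 72 × 21 + 648 × 28 = 19,656 days. From 72 hours: 72 × 18 + 648 × 25 = 17,496 days. Rates: 3.66 and 4.12 per 1000 days. Ratio 0.890.

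The understatement is about 11%. The ratios are the same for 1350 infants.

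**Step 2. Let entry vary.** For infants without an event, true at-risk time is 28 minus the mean of the later of entry and day 3. With entry uniform over 0-7 days that mean is (3/7) × 3 + (4/7) × 5 = 4.14, which leaves 23.86 days. The hand ratios agree closely with a simulation that includes the 10% of cases:

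| Entry uniform over | At-risk / birth clock | Simulated | At-risk / enrolment clock | Simulated |
|---|---|---|---|---|
| 0-1 day | 25/28 = 0.89 | 0.888 | 25/27.5 = 0.91 | 0.905 |
| 0-2 days | 25/28 = 0.89 | 0.888 | 25/27 = 0.93 | 0.922 |
| 0-3 days | 25/28 = 0.89 | 0.888 | 25/26.5 = 0.94 | 0.940-0.941 |
| 0-7 days | 23.86/28 = 0.85 | 0.845-0.846 | 23.86/24.5 = 0.97 | 0.972 |

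The understatement is therefore about 11-15% on the birth clock and about 3-10% on the enrolment clock. On the enrolment clock it is largest when infants enrol early; if all enrolled after 72 hours it would vanish.

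**Step 3. Does the same problem reach the Cox models?** In a simulation with an assumed true hazard ratio of 1.5 and no hazard before day 3:

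- Starting each infant at the later of entry and 72 hours gave the same hazard ratio as starting at entry (1.490 and 1.490 with entry unrelated to exposure; 1.488 and 1.488 with entry related to it). Risk sets form only at event times, and there are no events before 72 hours.
- Ignoring delayed entry changed nothing when entry age was unrelated to exposure (1.490 and 1.490).
- When exposed infants entered later (assumed days 2-7 against 0-2), the hazard ratio was 1.40 with a birth clock and no delayed entry, 1.52 with time since enrolment, and 1.49 on the age scale with delayed entry.

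The 72-hour window alone thus leaves hazard ratios unchanged. Bias needs entry age to be linked to the risk factor, together with a clock that mishandles it.

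**The case against.** The strongest defence is that the article never says follow-up starts at birth. The Demographic and clinical parameters section follows infants once recruited, so summed follow-up can naturally be read from recruitment, with no pre-enrolment time in it. The phrases about time at risk and new cases point the same way, and controls are defined by the absence of sepsis in an observation period qualified as after 72 hours of life. This largely stands as an argument against the 11-15% figure being the only one. It does not remove the point: the denominator is written out without a 72-hour start, and the enrolment reading still leaves about 3-10%.

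Three stronger readings are tempting, and the documents do not support them.

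- **That late entry is ignored and the Cox risk sets are misaligned.** The article says neither. It names no Cox time scale, a detail it may leave to the full plan.
- **That being outborn would look falsely protective, with a hazard ratio near 0.92.** This comes from 23/25 and needs outborn infants to enter on days 3-7 and a constant hazard from day 3. No section gives their entry age, and the Introduction puts the peak of LOS between the second and third week. With onset triangular over days 3-28 and a mode at day 14 (assumed), the share of events before entry averages (16/3)/(25 × 11) = 2%, a hazard ratio near 0.98. Time since enrolment can push the estimate the other way, as the 1.52 shows.
- **That the rate is 20-24% too low.** This needs a mean follow-up of about 12.5 to 14.7 days (3/14.7 = 20%, 3/12.5 = 24%). The article gives no such figure and plans weekly clinic visits and a day-28 call after discharge.

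**Conclusion.** The point holds for the incidence density. As written, the denominator counts time before 72 hours as at risk for an event that cannot occur then. The LOS rate is too low by about 3-10% with follow-up from enrolment and about 11-15% with follow-up from birth. These ranges rest on the article's 10% LOS, uniform entry over the first 1 to 7 days, follow-up to day 28, and no death or loss. The start of follow-up is also worded inconsistently across three sections.

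For the Cox models there is only a conditional risk: bias arises if entry age is related to a risk factor, such as place of birth, and the time scale does not handle entry.

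The severity is minor to moderate. The Statistical analysis section calls this its first objective, but the primary research question is dysbiosis before LOS. Neither that comparison nor the minimum of 42 per group uses person-time, and the rate can be corrected at analysis.

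**What to change.** 1. For LOS endpoints only, define at-risk time from the later of 72 hours of life and enrolment to the earliest of first LOS, death, end of ascertainment or day 28. Use it as the denominator of the incidence density. NEC and death have no 72-hour limit in their definitions, so their at-risk time should start at enrolment.
2. State that LOS with onset before enrolment is not counted as incident.
3. Reconcile the three descriptions of follow-up so that one origin and one end apply throughout.
4. Fit the Cox models on postnatal age with delayed entry at enrolment (for LOS, at the later of enrolment and 72 hours).

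The cost is wording. The survival package that the plan names handles delayed entry directly. The changes need only birth, enrolment and event times, and they add no visit, sample or participant.
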